### 2.9. Data Collection and Management

After recruiting participants, investigators and a professional coach will guide the training of participants and supervise them throughout the entire intervention period. Especially, participants will be required to return for a routine clinical examination every 4 weeks and monitor the participant's response through WeChat until the end of the study. As for the participants who discontinue or deviate from intervention protocols, investigators will call and WeChat participants to minimize data loss and participant withdrawal or loss during the study period.

Every participant should follow the instruction during the study period, and their related information should be recorded and stored as a print-based case report form (p-CRF). The electrical CRF should be stored in an encrypted mobile hard disk along with the procedure of filling in the p-CRF. All basic information of participants will be protected by the researching group, and a unique identified number will be applied during the procedure of the study. The mobile hard disk, p-CRF, and informed consent will be stored in the office of the Guang'anmen Hospital of the China Academy of Chinese Medical Sciences.

### 2.10. Data Monitoring

An independent Data and Safety Monitoring Board (DSMB) comprising two cardiologists and a statistician will monthly safeguard trial participants, monitor emerging trial data (including identifying any trends, such as increases in unexpected events), and pause the trial when necessary. The statistician of DSMB will also compare the data between the p-CRF and electrical CRF, and any modification of the data will be monitored and recorded in detail.

### 2.11. Statistical Analysis

This study will be based on intention to treat (ITT), and the results will be analyzed in accordance with the principle of ITT analysis. Statistical analysis will be performed at two prespecified time points and will be used to determine primary and secondary outcomes. Data from all patients who complete the follow-up will be analyzed according to the group in which they were originally defined. Participants who received reduced medication in the primary outcome analysis will be defined as those who received reduced medication during the exercise intervention and maintained it until the end of the study. The chi-square test or Fisher's exact test will be used to compare the proportion of patients with a primary outcome event between the two study groups. For the secondary outcomes, measurement data will be expressed as mean ± standard deviation (SD), and independence test, normality test, and homogeneity test of variance will be performed for each group. In addition, repeated measurements over time will be analyzed using analysis of variance (ANOVA of repeated measures), and pair comparisons between groups will be performed using the LSD *t*-test (homogeneity of variance) or Tamhane's T2 test (heterogeneity of variance). The composition of the gut microbiota will be analyzed using a nonparametric Mann–Whitney U test for relative bacterial abundance (at baseline and between groups). A Wilcoxon matched-pairs test will be used for comparison to analyze the differences in relative bacterial abundance between the Baduanjin and aerobic intervention groups. A *P*

-value of <0.05 will be taken to indicate a significant difference. All analyses will be performed using the SPSS v.17.0 software package. Every effort will be made to minimize data loss and participant withdrawal or loss during the study period; if the primary outcome or potential confounders' data are missing, a multiple imputation method will be used to fill in missing data.

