### 2.12. Safety Assessment

AEs may include medication withdrawal AEs (defined as the 10 most commonly reported AEs: stiff joints, pain, fatigue, loss of strength, breathlessness, sleep difficulties, pins and needles, sore eyes, dizziness, and impotence), exercise injury, and fall [27]. Serious AEs (SAEs) include, among others, prolonged hospital stay, disability, and death. AEs and SAEs will be recorded during the 12 weeks of intervention from enrollment. If either occurs during the study, the investigators will evaluate the relationship between the events and the intervention and report it to the Ethical Committee and DSMB; subsequently, they will decide whether the participant should withdraw from the trial.

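### Section 2.11 gives three unreconciled rules for who enters the primary analysis; read literally, the completer rule is not intention to treat

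*Protocol article*

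**What the plan says.** All three rules stand in one paragraph of the protocol article, section 2.11 (Statistical Analysis):

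- Principle: "the results will be analyzed in accordance with the principle of ITT analysis".
- Data analysed: "Data from all patients who complete the follow-up will be analyzed according to the group in which they were originally defined".
- Missing data: "if the primary outcome or potential confounders' data are missing, a multiple imputation method will be used to fill in missing data".

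The same section defines participants with a reduction as "those who received reduced medication during the exercise intervention and maintained it until the end of the study", and names the primary test: "The chi-square test or Fisher's exact test will be used to compare the proportion of patients with a primary outcome event".

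Three other sections bear on this:

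- Section 2.12 (Safety Assessment): after an adverse event has been assessed and reported, "subsequently, they will decide whether the participant should withdraw from the trial".
- Section 2.7.1 (Primary Outcome): high blood pressure or an adverse event after a reduction leads to readjustment of the medication.
- Section 2.9 (Data Collection and Management): participants who discontinue or deviate will be called and contacted by WeChat to limit data loss.

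**The concern.** The three rules do not give the same denominator. Intention to treat means all 70 randomised participants. The completer sentence, read literally, means those who reach the end of follow-up, kept in their original group. Multiple imputation of the primary outcome presupposes that participants without an outcome stay in the set, so it has little to do if they are left out. With no order among the rules and no named primary set, two analysts could defend different denominators for the same data.

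The choice matters because loss need not be unrelated to outcome. A participant lost before the end cannot be observed to have kept a reduction, and withdrawal from the trial can follow an adverse event, including those the protocol attributes to medication withdrawal. If such losses differ between arms, a comparison of completers is no longer a comparison of the groups as randomised.

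**Working it through.** **Inputs.** Section 2.8 plans 30 per arm before dropout, a 10% dropout allowance and 35 per arm randomised. The allowance reproduces: 30/(1 − 0.10) = 33.3, rounded up to 34 per arm or 68 in total, then raised to 70. Ten per cent of 70 is 7 participants. The protocol gives no split of dropout by arm.

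**Assumptions made here.** The split by arm, the event counts, and every dropout being a failure.

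**Effect on a proportion.** If x of 35 succeed and d failures are lost, the completer proportion is x/(35 − d). In terms of rates, a true success rate p becomes p/(1 − dropout rate). With equal dropout a null difference stays null, while a true difference is stretched (by 1/0.9 = 1.11 at 10% per arm). With unequal dropout the arm that loses more is favoured.

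**Test.** Uncorrected chi-square, N(ad − bc)² divided by the product of the four margins:

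- All randomised, 12/35 v 5/35: 70 × (12×30 − 23×5)² / (35×35×17×53) = 3.807, p = 0.051.
- Completers, 5 and 2 lost, 12/30 v 5/33: 63 × (12×28 − 18×5)² / (30×33×17×46) = 4.925, p = 0.026.
- Completers, 3 and 4 lost, 12/32 v 5/31: 63 × (12×26 − 20×5)² / (32×31×17×46) = 3.650, p = 0.056.

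| Lost (Baduanjin/aerobic) | Proportions | Difference (points) | Chi-square p | Fisher p |
|---|---|---|---|---|
| All randomised, missing = no reduction | 34.3% v 14.3% | 20.0 | 0.051 | 0.093 |
| 5/2 | 40.0% v 15.2% | 24.8 | 0.026 | 0.045 |
| 3/4 | 37.5% v 16.1% | 21.4 | 0.056 | 0.088 |
| 2/5 | 36.4% v 16.7% | 19.7 | 0.079 | 0.095 |

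The events are the same in every row; only the denominators change.

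**Type I error of a completers-only chi-square test**, for equal true success rates over all 35 v 35 randomised and all dropouts failures. The dropout splits shown all average 10%:

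| Dropout (Baduanjin/aerobic) | Common rate 10% | 25% | 40% |
|---|---|---|---|
| None | 0.057 | 0.048 | 0.048 |
| 10%/10% | 0.050 | 0.052 | 0.052 |
| 15%/5% | 0.052 | 0.061 | 0.070 |
| 20%/0% | 0.064 | 0.092 | 0.126 |

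Equal 10% dropout leaves the error rate near 5%. Marked inflation needs strongly unequal loss.

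**The case against.** The best defence is that the completer sentence does not contain the word only. Its main message may be analysis by original group, and with the imputation sentence it can be read as completers as observed, everyone else imputed. That reading is coherent. Imputation would not be idle even under the narrower reading, since it also covers confounders, which completers may lack. But the text does not settle on either reading, so the ambiguity stands.

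A reader might go further and infer that the completer rule removes failed reductions and so inflates the Baduanjin result. The documents do not support that, for these reasons:

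- Under section 2.7.1 an adverse event or high blood pressure leads to readjusted medication, not to leaving the trial. A reversed reduction in someone who stays is an observed failure and remains in the denominator.
- Section 2.12 also lists exercise injury and falls, which can occur in either arm without any reduction. Its wording leaves open whether the investigators alone decide on withdrawal.
- Nothing predicts the split of dropout. Loss mainly from the aerobic arm works the other way.
- The change from 0.051 to 0.026 compares completers with counting missing as no reduction, a rule that the protocol does not state. Multiple imputation by arm without strong predictors would centre near the completer proportions.
- The example is borderline by choice. Near the planned effect, 14/35 v 4/35 (p=0.006) and 14/30 v 4/33 (p=0.002) lead to the same conclusion. With Yates' correction, 12/30 v 5/33 gives p=0.053.

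All of this stands, and it limits the point to a possible bias of unknown direction. How to pool the test over imputed data sets, and what enters the imputation model, can be left to the statistical analysis plan and are not criticised here.

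**Conclusion.** The point holds as an unresolved conflict within section 2.11 over the primary analysis set. The literal completer rule contradicts the declared intention-to-treat principle and leaves the promised imputation of the primary outcome with little purpose.

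The consequence is a possibility, not a demonstrated bias. Within the planned loss of 7 of 70, the same 12 and 5 events give a difference between 19.7 and 24.8 points and a chi-square p between 0.026 and 0.079 across the splits shown. This rests on the assumed splits, on all dropouts being failures and on a result close to the threshold. It is enough to show that the denominator should be fixed in advance; it does not show that the trial will favour Baduanjin.

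**What to change.** - In section 2.11, replace the completer sentence with: *all randomised participants will be analysed in their assigned group*.
- Seek the week-12 prescription from every participant, including those who discontinue, through the calls and WeChat contact already planned in section 2.9.
- Score a participant whose reduction is known to have been reversed as not meeting the outcome, as the existing definition in section 2.11 implies.
- Apply the stated multiple imputation to outcomes that are still missing. Report two sensitivity analyses: missing counted as no reduction, and completers only.
- Reconcile sections 2.11 and 2.12 so that withdrawal after an adverse event does not take the participant out of the primary analysis set. This concerns the analysis set and outcome data only; no clinical rule on stopping the exercise is proposed.

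The cost is a few sentences in two sections and one prescription check per dropout, about seven at the planned rate. The sample size does not change.

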### 2.4. Randomization

Each participant will be randomly assigned to either the Baduanjin exercise group or the aerobic exercise group at a ratio of 1 : 1. The allocation sequence will be generated by the SAS software v.9.4 PLAN program and managed by an independent statistician who will not anticipate in the recruitment, evaluation, and intervention of participants. The statistician will put the list in a sealed, opaque, sequentially numbered envelope and give it to the investigators after sealing. Participants will be recruited in a natural, unpredictable order. After screening, the investigator will open an envelope sequentially to obtain a random number and determine whether the participant will be exposed to Baduanjin exercise or not.

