### 2.7. Outcome Measurements

Table 1 outlines the primary and secondary outcomes to be undertaken during the study. The primary outcome will be examined at postintervention (week 12). The secondary outcomes will include office BP, 24-h ambulatory blood pressure monitoring, health-related quality of life, and gut microbiota composition, all of which will be measured at baseline (week 0) and postintervention (week 12).

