*(4) Composition of Gut Microbiota*. Fecal samples will be collected for subsequent examination, and microbial composition will be analyzed via high-throughput 16S rRNA gene sequencing. We will advise participants not to receive any antibiotics for at least 1 month before sample collection and not consume any food containing probiotics (e.g., yogurt) for 7 days before sample collection.

The 24-h collection kit includes four gel ice packs (Techni Ice), collection bags, and fecal collection instructions and will be provided for fecal sample collection. Research assistants will also give participants detailed oral instructions before they collect fecal samples. In our laboratory, the cool bag will be maintained at 4°C, which has no significant effect on fecal microbiota diversity or composition [31]. Each sample will be stored briefly in a personal collection kit at 4°C and transported to the Guang'anmen Hospital within 24 h. Once at the hospital, the samples will be taken to the laboratory, where they will be aliquoted and stored at −80°C for subsequent analysis of intestinal microbial composition. All microbial community genomic DNA extractions will be performed using the E.Z.N.A.® Soil DNA Kit (Omega Bio-tek, Norcross, GA, USA).

The hypervariable region V3-V4 of the bacterial 16S rRNA gene will be amplified with primer pairs 338F and 806R using an ABI GeneAmp® 9700 PCR thermocycler (ABI, CA, USA) to obtain a polymerase chain reaction (PCR) product. The PCR product will then be purified and quantified, and the library will be constructed. High-throughput sequencing will be performed using the Illumina MiSeq platform (Illumina, San Diego, USA). The raw 16S rRNA gene sequencing reads will be demultiplexed, quality-filtered using Trimmomatic, and merged by FLASH. Operational taxonomic units (OTUs) will be clustered using UPARSE (version 7.1, http://drive5.com/uparse/), and the Quantitative Insights Into Microbial Ecology (QIIME) software will be used to analyze changes in relative bacterial abundance and *α* and *ß* diversity.

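### Two incompatible tests are named for the between-group comparison of bacterial abundance, and one of them, the Wilcoxon matched-pairs test, does not fit two unmatched randomised arms

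*Protocol article*

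**What the plan says.** All of the analysis text is in section 2.11 of the protocol article. For gut microbiota it plans an analysis "using a nonparametric Mann–Whitney U test for relative bacterial abundance (at baseline and between groups"). The sentence that follows reads: "A Wilcoxon matched-pairs test will be used for comparison to analyze the differences in relative bacterial abundance between the Baduanjin and aerobic intervention groups". Both sentences concern the same variable, and both speak of a comparison between the two groups.

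Three other statements bear on the choice of test:

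- Section 2.4 on allocation: "Each participant will be randomly assigned to either the Baduanjin exercise group or the aerobic exercise group at a ratio of 1 : 1". No matching of participants is described anywhere.
- Section 2.7 on timing: "gut microbiota composition, all of which will be measured at baseline (week 0) and postintervention (week 12"). Each participant therefore supplies one pair of samples, before and after.
- Section 2.7.2 on the aim: the QIIME software "will be used to analyze changes in relative bacterial abundance and" diversity.

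Section 2.7 lists gut microbiota composition last among the secondary outcomes.

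**The concern.** A matched-pairs test works on within-pair differences, so each value in one arm must belong with a particular value in the other. Individual randomisation to two parallel arms creates no such link. An analyst who follows the sentence has to invent the pairs, for instance by row order in the data file, and the result then depends on that invention.

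The text also gives no rule for which of the two tests governs. If they disagree, the choice would be made after the data are seen. What is at stake is the between-group result for a listed secondary outcome, on which the Discussion bases its exploration of mechanism.

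**Working it through.** The article gives no microbiota figure to reproduce. The check is of whether the named test fits the design and of what following it would cost.

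**1. Fit to the design.**

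| Comparison | Pairing in the design | Suitable rank test | What section 2.11 says |
|---|---|---|---|
| Between arms | None (section 2.4) | Mann–Whitney U | Mann–Whitney U, then also Wilcoxon matched-pairs |
| Week 0 to week 12 within a participant | Yes (section 2.7) | Wilcoxon matched-pairs | No test clearly assigned to abundance |

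The paired test is attached to the unpaired comparison, and the only paired comparison is left without a clear test.

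**2. Can it be computed?** A matched-pairs test needs equal numbers. Section 2.8 plans 35 per arm and allows 10% for dropout. Assume that each participant is lost independently with probability d. The chance of unequal arms is then 1 − Σₖ [P(K = k)]², where K is binomial(35, d):

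- d = 5%: 77%
- d = 10%: 84%
- d = 15%: 87%

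The multiple imputation in section 2.11 is stated for the primary outcome and potential confounders, so on the text it would not replace missing stool samples.

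**3. Dependence on ordering.** One data set was simulated with 35 per arm, lognormal abundances, log-scale SD 1 and a shift of 0.5 SD. The values of one arm were re-ordered at random 5,000 times and the signed-rank test was recalculated each time:

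- full range of P: 0.00003 to 0.075
- central 95% of P: 0.0012 to 0.037
- share of orderings with P < 0.05: 99.6%
- Mann–Whitney P, which does not depend on order: 0.0045

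In this data set most orderings agree on significance, but P for identical data varies by more than three orders of magnitude (0.075 / 0.00003 = 2,500) and can fall on either side of 0.05.

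**4. Type I error and power.** For each setting 10,000 trials were simulated with lognormal abundances, log-scale SD 1 and arbitrary pairing. The non-zero shift of 0.7 SD is an assumption.

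| Per arm | Log-shift | Signed-rank rejects | Mann–Whitney rejects |
|---|---|---|---|
| 30 | 0 | 4.9% | 4.6% |
| 35 | 0 | 5.0% | 4.9% |
| 30 | 0.7 SD | 67.7% | 73.7% |
| 35 | 0.7 SD | 74.2% | 80.6% |

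The loss of power is 73.7 − 67.7 = 6.0 points at 30 per arm and 80.6 − 74.2 = 6.4 points at 35. At 35 per arm the two tests disagreed on significance in 12% of trials with the shift and in 3.6% without it. Type I error is not inflated.

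**The case against.** The best defence is that a valid between-group test is already in the plan. The Mann–Whitney sentence suits two independent arms, can be computed with unequal numbers and, applied to week-12 values, is a legitimate randomised comparison. The Wilcoxon sentence may simply be a garbled description of within-group change, since that is the only pairing available. This stands to a large extent: the microbiota plan contradicts itself but is not invalid as a whole. It does not remove the point, because the sentence as printed names the two groups as the things compared, and nothing says which test governs.

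A reader might infer three stronger things, none of which the document supports.

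- *That the matched-pairs test will produce false-positive taxa.* With arbitrary pairing it rejects in 4.9% to 5.0% of null trials. Its faults are arbitrariness and lost power.
- *That every taxon will be tested at 0.05 without adjustment.* Section 2.11 gives one general rule, that a P "value of <0.05 will be taken to indicate a significant difference". It states neither a number of taxa nor a taxonomic level. If m independent null taxa were each tested at 0.05, the chance of at least one false positive would be 1 − 0.95^m, or 40% for m = 10 and 92% for m = 50. But m is not given, relative abundances are not independent of one another, and a multiplicity policy may sit in an analysis plan that is not shown.
- *That group differences will be read off from separate within-arm p-values.* If both arms truly changed equally and each within-arm test had power p, exactly one would be significant with probability 2p(1 − p), which is 32% at p = 0.2 or 0.8 and 50% at p = 0.5. No section says that this will be done, so it is only a practice for the revised text to rule out.

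**Conclusion.** The point holds in a limited form. Section 2.11 assigns two incompatible tests to one comparison, and the matched-pairs test is wrong for unmatched arms. That conclusion rests on the text alone. Followed literally, the sentence gives either an analysis that cannot be run or a p-value that depends on row order, at a cost of about 6 points of power. The power figure assumes lognormal abundances and a shift of 0.7 SD. The range of P comes from a single simulated data set, so it illustrates the dependence on order and does not estimate its usual extent. The chance of unequal arms assumes independent dropout.

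The severity is minor to moderate: the outcome is secondary, and the primary outcome, its chi-square or Fisher test and the sample size are untouched. That the article does not describe multiplicity control across taxa is not counted as an error.

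**What to change.** Replace the two microbiota sentences in section 2.11 so that each test has one job:

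- **Between groups:** Mann–Whitney U as the only test, preferably on each participant's week-12 minus week-0 change, which matches the aim in section 2.7.2 of analysing changes. Using week-12 values alone would also be valid. Either way the quantity compared should be named.
- **Within groups:** Wilcoxon matched-pairs on week 0 against week 12, labelled descriptive, with a statement that no group difference will be inferred from within-arm p-values.

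If many taxa are to be tested, false discovery rate control across taxa is an advisable addition, in the analysis plan if it is not already there. It would reduce the number of taxa called significant.

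The cost is two sentences, with no new data and no change to sample size or visits. An analysis of change needs both samples from a participant, so the text should say how a participant with only one is handled.
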